#### Incidence of malaria infection

The incidence of malaria infection was measured using active surveillance in a population-based cohort from the intervention and control clusters. At each cross-sectional survey, a sub-sample of individuals were recruited from both the control and intervention arms to measure the incidence of *P. falciparum* infection over time. From within the 20 compounds in each of the 20 clusters included in the cross-sectional survey, 33 individuals were randomly selected for a total sample size of 660 individuals (330 control and 330 intervention) aged ≥1 year. At the time of recruitment, all cohort participants were provided an LLIN and tested for malaria, and were treated with artemether–lumefantrine for malaria to clear subpatent infections. Cohort participants made scheduled monthly visits to the closest study health facility, and were encouraged to attend the health facility in case of illness. At both scheduled and sick visits, participants were administered a questionnaire on recent history of fever, health-seeking behaviour, LLIN use, and medication use in the month since the previous visit. Blood samples were obtained by finger pricks at each scheduled and sick visit for malaria testing by RDT and microscopy, and haemoglobin testing using a HemoCue^®^. A blood spot was also dried on a Whatman 903 filter paper for testing by rRT-PCR. Treatment decisions were made according to RDT and Hemocue^®^ results. All blood smears were read within 24 h of the visit, and participants whose blood smears were positive and discordant with the RDT result were contacted by study staff and treated.

Cohort participants not arriving for a scheduled visit were called and reminded to visit. Study staff made home visits to evaluate participants who were unreachable or who were unable to come to the clinic. Attempts to contact participants were ceased if they failed to present to three consecutive scheduled monthly visits, but they were not withdrawn from the cohort.

The sample size for the cohort study was based on detecting a relative difference in the incidence of malaria infection of at least 30% between the intervention and control arms over two years of follow-up. Based on data from previous studies, a baseline of 1.6 malaria infections per person per year, and a coefficient of variation of 0.25 were estimated for this study. A type I error rate of 5 and 80% power were used resulting in a sample size of 330 individuals per arm for a total sample size of 660 [45].

#### Incidence of clinical malaria

The incidence of clinical malaria from passive surveillance between residents of intervention and control clusters was compared. All persons registered with the HDSS and living within the core areas of clusters were considered under surveillance. Patients attending one of the 10 study health facilities were interviewed by study staff, who used laptop computers to determine if the patient was registered with the HDSS and lived in the study area. Patients not registered with the HDSS, but meeting criteria for HDSS registration [34] were asked for consent to participate, and their data were included in the study. For eligible patients, study staff recorded data from the clinical register into laptop computers, including history of fever/suspected malaria, malaria confirmatory testing and results, and medications prescribed. Per national guidelines, all patients presenting to a health facility with history of, or current fever, were considered suspected clinical malaria cases, were diagnosed by either RDT or blood smear microscopy, and were treated according to Kenya Ministry of Health Guidelines [44]. Data were retrieved from each of the 10 health facilities on a weekly basis.

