### Study design

The study was designed as a three-arm cluster-randomized controlled trial. Blinding of study participants or study staff to the intervention was not considered feasible or ethical. Ten of the 61 health facilities within the HDSS in Siaya County were purposively selected based on the following criteria: (1) high absolute malaria caseloads, (2) proximity of the facility to major roads for transport of supplies and samples, (3) government owned and run, and (4) minimum overlap with other known interventional/observational studies in the facility catchment; health facilities were chosen to maximize the distance between them, and all were at least 5 km from the next nearest health facility. All villages whose midpoint was located within 3 km of each health facility were included in the study. The villages surrounding each health facility were divided into three clusters along village boundaries such that the population was approximately evenly divided. One of the three clusters surrounding each health facility was randomly selected for the intervention, and the remaining two served as controls (Fig. 1). The purpose of the second control cluster was to allow the possible addition of a second intervention in the future. As no additional intervention arm was included in the study, for analysis purposes, the two control clusters were merged so that the study comprised 10 intervention and 10 control clusters with equal sample sizes. To reduce contamination between intervention and control clusters, the sampling frame for evaluations were limited to a core area within each cluster. The core area was defined as an area within the cluster that was ≥300 m from the perimeter of the cluster. The 300 m distance was chosen on the basis of previous studies at the site that indirectly demonstrated that the mass effect of a community based intervention (LLINs) extended to approximately 300 m based upon both entomologic [40] and epidemiologic [41] data. The area between the core and the perimeter of the cluster was defined as the buffer; though the intervention was performed in the buffer, data from individuals residing within the buffer area were not used for evaluations.

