#### Prevalence of malaria infection

Population-based cross-sectional surveys were performed annually during the peak malaria transmission season in July to estimate the point-prevalence of malaria parasitaemia and anaemia. Twenty compounds from within the core areas of each of the 20 clusters were randomly selected from the most recent HDSS housing roster for inclusion.

CHVs visited each selected compound and enrolled all residents. A questionnaire was administered to each participant, or their caregiver, which included information on demographic characteristics, risk factors for malaria infection, history of illness, health care-seeking, and costs associated with illness episodes. A blood sample was obtained using finger or heel prick to measure haemoglobin (HemoCue^®^; Ängelholm, Sweden) and malaria parasitaemia by RDT. Additionally, thick and thin blood smears were prepared for malaria microscopy and a blood spot was dried on Whatman 903 filter papers for molecular tests (Table 2). Based on RDT results, CHVs followed a treatment and referral algorithm programmed on the PDAs and tablets that evaluated the participant’s potential pregnancy status and history of allergies/adverse reactions (Fig. 2).

**Table 2 Tab2:** Sample collection by evaluation method

Collection activity	Age group	Sampling	Arm	Collection location	Samples collected and diagnostics conducted
Cross-sectional surveys	≥1 month old	20 compounds from the core area per cluster	Both	Household	RDT Blood smear Dried blood spots Hemoglobin
Cohort visits (scheduled and unscheduled)	≥1 year old	Random selection from cluster cores during baseline and year 1 XSS	Both	Health facility	RDT Blood smear Dried blood spots Hemoglobin
MTaT rounds	≥1 month old	All residents	Intervention	Household	RDT Dried blood spot (from first 5000)
Passive surveillance	All ages	All individuals living within the core area of a cluster	Both	Health facility	RDT

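### Cohort members are counted in passive surveillance and form about twice the share of the intervention population, so any difference in their recorded clinical-malaria rate does not cancel between arms; sign unknown, size probably a few per cent

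*Protocol article*

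**What the plan says.** All references are to the protocol article.

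- **Who is under passive surveillance.** Incidence of clinical malaria: "All persons registered with the HDSS and living within the core areas of clusters were considered under surveillance". The passive-surveillance rows of Tables 1 and 2 likewise admit core residents without any cohort exception. Under Data analysis, an arm's confirmed cases at each facility per month are divided by that arm's whole population in the facility catchment.
- **What counts as a passive case.** A patient at a study facility with current or past fever and a positive RDT or smear, taken from the facility's clinical register (Incidence of clinical malaria; Data analysis).
- **What cohort members do.** Incidence of malaria infection: "Cohort participants made scheduled monthly visits to the closest study health facility, and were encouraged to attend the health facility in case of illness". At each visit they are asked about recent fever and tested. At recruitment they receive a net and clearing treatment.
- **Cohort size.** The same section selects 33 people per cluster, "for a total sample size of 660 individuals (330 control and 330 intervention) aged ≥1 year".
- **Population of each arm.** Study design: villages around each facility were "divided into three clusters along village boundaries such that the population was approximately evenly divided". Then: "One of the three clusters surrounding each health facility was randomly selected for the intervention, and the remaining two served as controls". For analysis, "the two control clusters were merged so that the study comprised 10 intervention and 10 control clusters with equal sample sizes".

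**The concern.** Clinical-malaria incidence is among the primary objectives, and passive surveillance is the data source that measures it. Its value lies in recording care-seeking that the trial did not prompt. Cohort members are a group whose visits, testing and treatment the trial does prompt, at the very facilities where passive cases are counted. A sick visit, or a scheduled visit with reported fever and a positive test, could meet the passive case definition.

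If the cohort were the same fraction of each arm and its members' relative rate were the same in both arms, the effect would drop out of the rate ratio. Here the fraction differs by design, because equal cohort numbers are drawn from populations in a ratio of about 1:2. Part of the estimated effect on clinical malaria could then reflect the cohort's procedures and not mass testing and treatment.

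**Working it through.** **1. The plan's own figure.** 33 per cluster × 10 clusters = 330 per arm, and 2 × 330 = 660, as stated. This agrees with the stated sample-size inputs. With rates of 1.6 and 1.12 per person-year (a 30% reduction), coefficient of variation 0.25, two-sided 5% (assumed), 80% power and 33 × 2 = 66 person-years per cluster:

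clusters per arm = 7.849 × [(1.6 + 1.12)/66 + 0.25² × (1.6² + 1.12²)] / 0.48² = 9.53

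This rounds to 10 (10.53 if the usual one cluster is added). The point below uses only the 33 per cluster.

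**2. Cohort share by arm.** Let N be the core population of one original cluster.

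- Intervention: s_I = 33/N.
- Control (merged pair): s_C = 33/(2N).
- s_I/s_C = 2.0 whatever N is, if cores scale with cluster populations.

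If the 300 m buffer were redrawn around the merged control pair (an idealised 3 km circle at even density), the core would be about 72% of the control area and 64% of the intervention area. The ratio would then be about 2.2.

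**3. Distortion.** Let R be the recorded clinical-malaria rate in cohort members relative to other core residents, taken as equal in both arms. An arm's rate is multiplied by 1 + s(R − 1), so the intervention/control rate ratio is multiplied by

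F = [1 + (33/N)(R − 1)] / [1 + (33/(2N))(R − 1)]

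**4. Assumed N.** The article gives no core population. A crude pro rata figure is 220,000 × 10/61 = 36,066 around the ten facilities. One third is 12,022, and 64.4% of that in the core is about 7,740, or roughly 770 per cluster. A range of 500 to 3,000 is shown around it.

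**5. Results.** R has no source in the documents. R = 0 stands for cohort visits that never reach the register while members stay in the denominator.

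| N per cluster | Share, intervention / control | R = 0 | R = 0.5 | R = 2 | R = 3 | R = 5 |
|---|---|---|---|---|---|---|
| 500 | 6.6% / 3.3% | 0.966 | 0.983 | 1.032 | 1.062 | 1.117 |
| 770 | 4.3% / 2.1% | 0.978 | 0.989 | 1.021 | 1.041 | 1.079 |
| 1,000 | 3.3% / 1.65% | 0.983 | 0.992 | 1.016 | 1.032 | 1.062 |
| 3,000 | 1.1% / 0.55% | 0.994 | 0.997 | 1.005 | 1.011 | 1.022 |

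Worked line: N = 770 and R = 5 gives (1 + 0.0429 × 4)/(1 + 0.0214 × 4) = 1.171/1.086 = 1.079. With the redrawn buffer (ratio 2.24), N = 770 gives 0.976 at R = 0 and 1.088 at R = 5.

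**6. On the scale of an effect.** The article states no target effect for clinical malaria. Borrowing the cohort's 30% reduction as illustration, a true ratio of 0.70 at N = 770 would read as 0.685 (R = 0), 0.715 (R = 2) or 0.755 (R = 5).

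**7. With cohort members excluded.** With s_I = s_C = 0, F = 1.00.

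**The case against.** The strongest reply is that this rests partly on silence in a condensed article. The four evaluations are introduced as separate strategies. Cohort visits have their own questionnaire and a fuller sample set, while passive data come from the clinical register. Nothing says that cohort visits are written into that register, and a rule for overlapping records may sit in the full protocol or analysis plan. Several cohort contacts could not produce a passive case anyway: home visits are not facility attendances, and a positive test without fever does not qualify. The article reports that over 90% of microscopy-positive residents in many age groups had no recent fever.

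Most of this stands. A reader might infer that trial-driven visits do bias the clinical-malaria comparison, and in particular that they hide a real benefit. The documents do not support that. It would need cohort visits to be in the register and members' recorded rate to exceed their neighbours', whereas the net, clearing treatment and repeated testing point the other way.

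A reader might also infer a second cohort of 33 per cluster that doubles the effect, since Table 2 describes "Random selection from cluster cores during baseline and year 1 XSS". Table 1 and the sample-size text give 330 per arm, and nothing says that this number applies to each round or that follow-up overlaps.

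What the reply does not remove is the stated denominator. It covers the arm's whole population, so cohort members are in it whether or not their visits are counted. If visits bypass the register, members contribute person-time but few or no cases, again in unequal shares. Nor does the equal-sample-size wording for the merged arms help, because Table 1 gives no sample size for passive surveillance: it takes all core residents.

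**Conclusion.** The point holds as a risk of unequal ascertainment, not as a demonstrated bias. The text includes cohort members in the clinical-malaria incidence, and their share is about twice as large in the intervention arm. Whether this moves the rate ratio, and in which direction, cannot be told from the article.

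The size is probably a few per cent: a multiplier of about 0.98 to 1.08 at 770 core residents per cluster for R from 0 to 5, and 0.97 to 1.12 over the whole grid. A shift above 10% needs the smallest assumed core together with the largest assumed R. The calculation assumes clusters of about equal population, cores that scale with them, 33 cohort members per analysis cluster, and the same R in both arms. It is unlikely on its own to reverse a conclusion, but it is avoidable at little cost in a primary-objective outcome.

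**What to change.** In Incidence of clinical malaria and in Data analysis, with matching entries in the passive-surveillance rows of Tables 1 and 2, state that cohort members are left out of the clinical-malaria incidence from enrolment to the end of their follow-up, in both arms. Remove their cases from the monthly numerator and their person-time from the HDSS denominator. Since members who stop attending are not withdrawn, the end of follow-up needs a fixed definition. State also whether cohort visits are entered in the clinical register. If the main analysis must keep all core residents, report the exclusion as a sensitivity analysis.

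**Cost.** One sentence and one linkage step, which can be done retrospectively: the cohort was drawn from compounds on the HDSS roster, and passive-surveillance staff already check HDSS registration. The lost person-time is 33/N in the intervention arm and 33/(2N) in control, about 4.3% and 2.1% at N = 770 (6.6% and 3.3% at N = 500). Because the cohort leaves out infants under one year and women pregnant at recruitment, removing it shifts the remaining age mix very slightly. At these shares that is a minor price.

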#### Entomological transmission indices

Monitoring was conducted to assess the impact of MTaT on entomological indices of malaria transmission by comparing the proportion of *Anopheles* mosquitoes with *P. falciparum* sporozoite and oocyst infections, and the parity rate, by study arm.

Each month, a simple random sample of twelve and six houses were selected (without replacement) from each of the ten control and intervention clusters, respectively, for pyrethrum spray catches (PSCs). Briefly, white sheets were placed over the surface of the floor and furniture between 0600 and 1200 h, and two collectors (one inside and one outside the house) sprayed around the eaves with 0.025% pyrethrum emulsifiable concentrate with 0.1% piperonyl butoxide in kerosene. The collector inside the house then sprayed the roof and walls of the house, and the house was closed for 10–15 min. Dead mosquitoes were then collected and placed on moist filter paper inside of petri dishes and returned to the laboratory.

Live collections using Prokopack [46] aspirators were performed for one week each month in each study arm. During the live sampling week, collectors visited as many households as possible until 1200 h. To maximize the number of specimens collected, the live collection methodology did not use a random sample. In each house, collectors spent 15–20 min aspirating mosquitoes, and those collected from the same house were placed into a single cage.

#### Costing

During cross-sectional surveys, socioeconomic variables and data on household costs associated with care-seeking and treatment of febrile illnesses and malaria, including missed days of work and/or school, were collected. Socioeconomic variables were used to establish wealth quintiles. These data will be compiled to evaluate costing and differences in equity impact of the intervention. Additionally, during MTaT rounds, data for cost of the intervention per population reached were collected to evaluate cost-effectiveness and gained cost-efficiencies throughout subsequent rounds. Costs will be categorized as either intervention or research costs in order to evaluate potential programmatic delivery costs.

### Laboratory methods

#### Preparation of dried blood spots

Five blood spots were prepared, each with a minimum of 50 mm^3^ of blood, into each spot of a Whatman 903 filter paper, and were dried overnight at room temperature. Each filter paper was sealed tightly in a plastic bag with desiccants and a moisture indicator, and was transported to a central laboratory for storage at −80 °C until use.

#### Measurement of hemoglobin

Haemoglobin level was determined using portable HemoCue^®^ analyzers (HemoCue^®^ AB, Angelholm, Sweden). All HemoCue^®^ analyzers were validated through comparison to an automated Coulter Counter (Beckmann-Coulter, IN, USA) before the study and calibrated on a monthly basis using low, normal, and high hemoglobin controls supplied by the manufacturer.

#### Malaria microscopy

Thick and thin blood smears were transported to a central laboratory at Siaya County Referral Hospital daily. Blood smears were stained with 10% Giemsa, dried for 15 min, and examined for the presence of malaria parasites under oil immersion. A smear was considered negative if no parasites were found in 100 microscopic high powered fields. If positive, malaria parasites were counted against 500 white blood cells (WBC) and parasite densities were expressed per mm^3^ of blood using an assumed 8000 WBCs/mm^3^ [47–49]. All blood smears were independently read by two microscopists blinded to the other’s read, and to the participants’ study arm, who had adequately passed an external quality assurance programme provided by the National Institute of Communicable Diseases, South Africa [50]. Discordant reads, defined as reads that differed qualitatively, by species, or with a difference in parasite density of ≥50%, were confirmed by a third microscopist blinded to the results of the first two microscopists.

#### Real-time reverse transcriptase polymerase chain reaction for malaria

Real-time reverse transcriptase polymerase chain reaction was used with randomly selected RDT negative samples from the MTaT rounds to estimate the number of infections missed by RDTs. Briefly, commercially available TaqMan Universal Master Mix (Applied Biosystems, CA, USA) and species-specific probes corresponding to *P. falciparum*, *Plasmodium vivax*, *Plasmodium malariae*, and *Plasmodium ovale* were used to detect the presence of parasites. A threshold cycle number (Ct) of 40 was used as the cut-off. Similarly, randomly selected samples that were positive or negative for asexual parasites were used to determine the presence of stage V gametocytes using nucleic acid sequence based amplification (Pfs25-NASBA) assays as previously described [51].

#### Laboratory testing of mosquitoes

Mosquitoes collected during PSCs and live collections were first identified to species using morphological keys [52], while sibling species were identified by rRT-PCR for all *Anopheles gambiae s.l*. [53] and a subset of *An. funestus s.l*. [54] for the rRT-PCR identification of *An. gambiae s.l*., only the universal, the *An. gambiae s.s*. and the *An. arabiensis*, primers were used as these two species are the only ones known from this area. A subset of freshly collected, unfed mosquitoes were dissected and examined for parity status [55]. Fed, gravid and half-gravid mosquitoes were held for 5–10 days and midguts were dissected, stained with mercurochrome and then examined at 100× for the presence of oocysts. *P. falciparum* sporozoite rates in *Anopheles* mosquitoes were determined by sandwich ELISA [56, 57].

### Data analysis

The primary outcome of incidence and prevalence analyses, in the cohort and cross-sectional studies, respectively, were microscopically confirmed *P. falciparum* parasitaemia. Arm-specific unadjusted prevalence ratios (PR) for parasitaemia and anaemia were calculated using data from the series of pre- and post-intervention cross-sectional surveys. These data were analyzed with a log-binomial model using generalized estimating equations to account for clustering. Pre- and post-intervention PRs between arms were evaluated using the same model. The incidence of clinical malaria, diagnostically confirmed by either RDT or microscopy, presenting to the MTaT study health facilities (passive surveillance) was calculated. Total case counts originating from each study arm at each health facility per month was divided by the total population of the study arm residing in the catchment area of the health facility according to the HDSS. The incidence of infection was determined from the cohort data. A Cox-Proportional Hazards model was used to compare time to infection between arms. Adjusted models were created to account for confounders including socioeconomic status, anti-malarial use, and LLIN use. Socioeconomic status (SES) was assessed using principal component analysis models of household assets [58]. Sporozoite and oocyst rates were compared by logistic regression using generalized estimating equations to account for correlated observations within the households. All analyses were performed using SAS statistical software version 9.3 (SAS Institute, Carey, NC).

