The sample size was calculated, assuming a malaria prevalence of 40% in the control arm, a type I error rate of 5, and 80% power, to detect a relative difference in malaria prevalence of at least 50% between arms by study end. For ease of sampling, compounds were selected, and all individuals in the compounds were enrolled. A conservative coefficient of variation of 0.3 for between-cluster and—compound variance was used. Twenty compounds were selected per cluster for a total of 400 compounds across the study area (200 in each arm), and a total population of approximately 2000 individuals [45].

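### The prevalence analysis lists unadjusted within-arm before-after ratios first and leaves the between-arm comparison ambiguous; a baseline-adjusted ratio between arms at the final survey should be primary

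*Protocol article*

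**What the plan says.** All references are to the protocol article. Under Data analysis, the first prevalence analysis named is: "Arm-specific unadjusted prevalence ratios (PR) for parasitaemia and anaemia were calculated using data from the series of pre- and post-intervention cross-sectional surveys". The method follows: "These data were analyzed with a log-binomial model using generalized estimating equations to account for clustering". The between-arm comparison gets one sentence: "Pre- and post-intervention PRs between arms were evaluated using the same model". Later, after the Cox model for the cohort, the section adds: "Adjusted models were created to account for confounders including socioeconomic status, anti-malarial use, and LLIN use".

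The sample size, under Prevalence of malaria infection, was set on a different footing: "to detect a relative difference in malaria prevalence of at least 50% between arms by study end".

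A baseline survey exists. Table 2 names a baseline and a year 1 cross-sectional survey, with blood smears taken at the surveys, so cluster prevalence by microscopy before the intervention is available. Under Study design, one of the three clusters around each of ten facilities was randomised to the intervention, so allocation was within facility. The two control clusters were merged, giving 10 clusters per arm for analysis.

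**The concern.** A before-after PR within one arm contains MTaT and everything else that changed between two July surveys. Only the comparison between arms is protected by randomisation. If the within-arm ratios are read as the result, a significant fall in one arm and a non-significant fall in the other can be mistaken for an effect.

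The between-arm sentence has two readings:

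- **Ratio of PRs (arm by period).** This is a valid randomised contrast, but it carries the sampling noise of both surveys. It is also not the quantity on which the sample size was built.
- **A separate between-arm PR at each survey.** The final-survey PR matches the sample size target, but as described it is unadjusted. With 10 clusters per arm, a chance difference in baseline prevalence would pass into the estimate.

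Neither reading makes baseline cluster prevalence a covariate, although the data were collected.

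**Working it through.** **Inputs from the article.** Control prevalence, error rate and power: "assuming a malaria prevalence of 40% in the control arm, a type I error rate of 5, and 80% power" (two-sided 5% assumed). Planned effect: 50% relative, so 40% versus 20%. Variation: "A conservative coefficient of variation of 0.3 for between-cluster and" between-compound variance. Survey: "Twenty compounds were selected per cluster for a total of 400 compounds across the study area (200 in each arm"), about 2000 people in total, so about 100 per cluster. Table 1 gives 857 per arm, or 85.7 per cluster.

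**Assumed.** The correlation r between a cluster's baseline and final prevalence. The article gives none, so a range is shown.

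**The plan's own figure.** The Hayes-Bennett formula for unmatched clusters, with 10 per arm and these inputs, needs about 14.4 people per cluster, or 144 per arm. The 857 is therefore not reproduced. That is a separate matter; here it means only that the survey is larger than the stated target requires.

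**Variance relative to the unadjusted end-of-study contrast.** Ratio of PRs: 2(1−r). Baseline-adjusted: 1−r².

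- r = 0.3: 1.40 and 0.91.
- r = 0.5: 1.00 and 0.75.
- r = 0.6: 0.80 and 0.64.

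Since 1−r² = (1−r)(1+r) and 1+r ≤ 2, the adjusted contrast is never less precise than the ratio of PRs. Before the cost of degrees of freedom, it is also never less precise than the unadjusted end-of-study contrast. The ratio of PRs beats the unadjusted contrast only when r exceeds 0.5.

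**Power.** Power = Φ(√[(10−1)(p0−p1)²/(v × factor)] − 1.96), with v = [p0(1−p0)+p1(1−p1)]/100 + 0.09(p0²+p1²).

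Planned effect, p0 = 0.40, p1 = 0.20: v = 0.0040 + 0.0180 = 0.0220, and √(9 × 0.04/0.0220) = 4.05.

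Smaller effect for illustration, p1 = 0.28 (30% reduction): v = 0.004416 + 0.021456 = 0.025872, and √(9 × 0.0144/0.025872) = 2.24.

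| Effect | r | Ratio of PRs | End-of-study, unadjusted | Baseline-adjusted |
|---|---|---|---|---|
| 50% | 0 | 82% | 98% | 98% |
| 50% | 0.3 | 93% | 98% | 99% |
| 50% | 0.5 | 98% | 98% | >99% |
| 30% | 0 | 35% | 61% | 61% |
| 30% | 0.3 | 47% | 61% | 65% |
| 30% | 0.5 | 61% | 61% | 73% |
| 30% | 0.6 | 71% | 61% | 80% |

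With 85.7 per cluster, the lowest figure at the 50% effect (ratio of PRs, r = 0) is 80.5%: v = 0.02267, and √(9 × 0.04/(0.02267 × 2)) = 2.82.

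A second calculation on the log scale adds compound-level variation. It indexes correlation by the true cluster autocorrelation. At a 30% effect and autocorrelations of 0.2, 0.5 and 0.8, it gives 44%, 57% and 78% for the ratio of PRs, 64% throughout for the unadjusted contrast, and 65%, 71% and 84% for the adjusted one. The adjusted contrast again comes out best.

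**Within-arm PRs under no effect.** Suppose MTaT does nothing and prevalence falls 20% in both arms (40% to 32%), with 85.7 people in 20 compounds per cluster. The variance of a within-arm log PR is [(0.09+s0)+(0.09+s1)−2 × a × 0.09]/10, where s(p) = 0.09/20 + (1−p)/(85.7p) and a is the autocorrelation. Here s0 = 0.0220 and s1 = 0.0293. At a = 0.5 the variance is 0.0141. Then 0.223/0.119 = 1.88, and the chance that a within-arm PR is significant is 47%. It is 36% at a = 0.2 and 67% at a = 0.8. Treating the arms as independent, the chance that the intervention arm is significant and the control arm is not is 0.467 × 0.533 = 25% at a = 0.5, and 22% to 25% over the three values.

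**The case against.** The strongest reply is that a randomised comparison is already in the text. The between-arm sentence can be read as a PR at each survey, and the final one is then exactly the sample size target. That stands as one fair reading, and an unadjusted PR under randomisation is valid. It also stands that the planned effect is 50%. The 30% used for illustration is the cohort's incidence target, not a prevalence target, and no planned power is at risk.

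Three stronger readings are tempting, and the article does not support them:

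- **Prevalence rests on a non-randomised contrast, or baseline data go unused.** The between-arm sentence contradicts this.
- **The plan fixes a change-versus-change test and so loses power.** This is only one of two readings.
- **The adjustment list leaves out baseline prevalence and age.** The list is worded as non-exhaustive and follows the Cox sentence, so it may not concern prevalence at all. Full covariate lists are commonly left to an analysis plan.

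Nor is the precision free: it depends on an unknown correlation and spends degrees of freedom.

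The objection does not remove the point. The article describes the prevalence PRs as unadjusted, puts the before-after ones first and names none as primary. That is a stated choice, not missing detail.

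**Conclusion.** The point holds as a concrete improvement to a stated method. Within-arm before-after PRs cannot carry the inference, and the between-arm estimate should be fixed as one named quantity. Adjustment for baseline cluster prevalence protects against chance imbalance under the separate-PR reading. Under the ratio-of-PRs reading it improves precision.

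Against the unadjusted end-of-study contrast, variance falls by 9% at r = 0.3 and 25% at r = 0.5. At a 30% effect that takes power from 61% to 65% and 73%. At the planned 50% effect all versions exceed 80%, so this does not rescue planned power. It matters if the true effect is smaller, and the Discussion itself expects migration between clusters to pull results towards the null.

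The figures rest on assumed correlations, a coefficient of variation of 0.3 and normal approximations. They include no facility term.

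**What to change.** State as the primary prevalence estimate the between-arm PR for microscopically confirmed parasitaemia at the final survey. Adjust it for the cluster's baseline prevalence by microscopy and account for facility, within which clusters were randomised. Label the arm-specific before-after PRs descriptive. If an arm-by-period ratio of PRs was intended, say so and keep it as a supporting analysis.

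The cost is wording only; no new data are needed. Statistically, baseline prevalence spends one degree of freedom. Ten facilities entered as fixed effects spend up to nine more. With 20 clusters, a cluster-level analysis goes from 18 residual degrees of freedom to 17 with baseline alone, and to 8 with facility as well. The two-sided 5% critical value then rises from 2.10 to 2.31. Small-sample inference should therefore be specified. Whether facility terms repay their cost depends on within-facility correlation, which the article does not give.
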